### Statistical analysis

2.13

Analysis (using STATA or SPSS 28.00) will follow standard methods for trials using comparisons between the three groups. First, a study of the maturation trajectories of the infants will be carried out, with a description of the pre-post intervention changes in the tests carried out. Second, quantitative evaluations of joint attention data and molecular markers will be performed, detected, and described through the mean and standard deviation in the case of a Gaussian distribution of variables or the median and interquartile range in the case of a non-Gaussian distribution. The normality of distributions will be assessed by applying the Shapiro‒Wilk test. For categorical variables, absolute frequencies and percentages will be reported. Genetic analysis of intrafamilial allelic inheritance will be conducted by AFBAC (Affected Family-Based Controls) (55) and TDT (Transmission Disequilibrium Test) (56). The immunological parameters obtained from the groups of ASD children and TD children will be analysed using a nonparametric Mann‒Whitney test that will allow the identification of specific immunological biomarkers of ASD-associated neuroinflammation. Moreover, clinical parameters will be correlated with immunological biomarkers characteristic of ASD children. Finally, epigenetic analysis will allow us to define a panel of microRNAs that can differentiate between ASD children and children with typical development. Using computer algorithms, the potential targets, pathways, and biological functions deregulated by this group of miRNAs will be analysed. These data will also be analysed concerning the clinical parameters evaluated in the study and the genetic and inflammatory characteristics of the subjects studied.

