### Trial design

2.1

The study is a controlled trial following the Consolidated Standards of Reporting Trials (CONSORT) guidelines. After enrolment and baseline assessments (T0), the children will be allocated to one of three groups:
Group 1—Clinical Monitoring Group (CM): Siblings of TD children with no signs of concernGroup 2—Active Monitoring Group (AM): Siblings of ASD children with no signs of concernGroup 3—Early Intervention Group (EI): Siblings classified as “with signs of concern” at the baseline evaluation.

All children will be re-evaluated after 6 months (T1) and 12 months (T2) from T0. Figure 1 depicts the CONSORT flow chart.

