#### Biomolecular assessment

2.5.4

Biological samples from family quartets will be collected as follows:

Saliva samples will be collected using 3 different kits for DNA or RNA extraction and protein detection through spongy swabs inserted into the baby's mouth, leading to non-invasive, simple, fast, and, most importantly, painless saliva collection. Saliva samples will be collected from all the probands at T0, T1, and T2, as well as their siblings and parents at T0, to assess parent-to-child genetic transmission and the risk of ASD. If possible, a sample of approximately 40 ml of blood (from the parents) will be collected (see Supplementary Appendix 1).

On these samples, the following analysis will be performed:
•Genetic analysis will be conducted on all enrolled children, their older siblings, and parents using a next-generation sequencing (NGS) gene-targeted panel approach to analyse genes involved in synaptogenesis and immunogenetic regulation.•Epigenetic analysis of the miRNome in saliva collected from all enrolled children at all time points will be performed by NGS. Epigenetic analysis will allow us to define a panel of microRNAs that can differentiate between ASD children and children with typical development.•Analysis of inflammatory cytokines and neurotrophic factors using an automated immunoassay system (ELLA, Biotech) will be performed in probands at T0, T1 and T2. The parents will also be characterised for cytokine and lymphocyte subsets at T0.

Correlations between clinical parameters and all biological variables (genetic, epigenetic, inflammatory) will be performed to correlate molecular biomarkers with neurodevelopmental changes at follow-up and before and after intervention.

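### The cytokine and miRNA analyses are set as ASD versus TD children, but no study group is defined by ASD and the diagnosed older siblings are listed only for genetics

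*Protocol article*

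**What the plan says.** **The planned contrast.** Protocol article, section 2.13 (Statistical analysis): "The immunological parameters obtained from the groups of ASD children and TD children will be analysed using a nonparametric" Mann-Whitney test, which is expected to identify biomarkers specific to ASD-related neuroinflammation. The same section says that the epigenetic analysis will "define a panel of microRNAs that can differentiate between ASD children and children with typical development". Section 2.5.4 states the same miRNA aim.

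**Who is assayed.** Section 2.5.4 (Biomolecular assessment):
- miRNA: "Epigenetic analysis of the miRNome in saliva collected from all enrolled children at all time points will be performed by NGS".
- Cytokines and neurotrophic factors: "will be performed in probands at T0, T1 and T2". For adults, "The parents will also be characterised for cytokine and lymphocyte subsets at T0".
- Genetic panel: "Genetic analysis will be conducted on all enrolled children, their older siblings, and parents".
- Saliva collection: "Saliva samples will be collected from all the probands at T0, T1, and T2, as well as their siblings and parents at T0".

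**The study groups.** Sections 1, 2.1 and 2.11 define three groups of infants. Groups 1 and 2 have no signs of concern and differ in whether the older sibling is typically developing or has ASD. Group 3 is "Siblings classified as “with signs of concern” at the baseline evaluation". It is set by a Griffiths-3 quotient below 85 together with a CSBS-ITC concern score, and it may contain infants at low or high familial risk.

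**The concern.** A two-sample test needs two defined samples, and the pair named in section 2.13 does not correspond to any pair of study groups. Elsewhere the article uses ASD children and TD children mainly for the older siblings of the enrolled infants, and those siblings are not listed for cytokines or miRNA.

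An analyst following the text would have to improvise. One route is to relabel risk groups as ASD and TD. Differences linked to familial risk or to early developmental concern would then be reported as ASD biomarkers. The other is to build a case group afterwards from whichever infants meet ASD criteria at T2, in a number nobody planned for. In neither case would the result carry the conclusion announced in section 2.13.

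The contrast also has no time element, although part of H4 concerns the effect of the programme on epigenetic and immune measures and the infants are sampled at three visits.

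**Working it through.** **1. Match each assay to the people who receive it (section 2.5.4).**

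| Assay | Enrolled infants | Older siblings | Parents |
|---|---|---|---|
| Genetic panel | yes | yes | yes |
| miRNA | yes (T0, T1, T2) | not listed | not listed |
| Cytokines | yes (T0, T1, T2) | not listed | T0 |

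The term probands must mean the infants here. They are sampled at all three study visits, and their siblings are named separately, at T0 only. So no child with a known ASD diagnosis at enrolment is listed for cytokines or miRNA.

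**2. Match the groups to the contrast.** Groups 1 to 3 are formed at T0, in infants of at most 8 or 10 months (sections 2.2, 2.3 and 2.11), from sibling status, Griffiths-3 and CSBS-ITC. None is defined by an ASD diagnosis. Group 3 is not an ASD group: its entry rule concerns developmental quotient and screening concern, and low-risk infants can enter it.

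**3. Size of a case group if one were formed at T2.** No figure in the article bears directly on this, so the enrolment numbers in section 2.6 are used. They reproduce closely: with difference 0.8, SD 0.56 and two-sided alpha 0.01, the noncentral t gives power 0.792 at 13 per group and 0.831 at 14, hence 14. Allowing for 15% drop-out, 14 / 0.85 = 16.47, stated as 16 per group and 48 in total.

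The article gives no ASD rate for these infants, so 5% to 30% is assumed. The number of high-risk infants lies between 16 (Group 2 only) and 32 (Groups 2 and 3, if all of Group 3 is high-risk). Expected cases = infants × rate; chance of no case = (1 − rate)^infants.

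| Assumed rate | Expected cases, 16 infants | Chance of none | Expected cases, 32 infants | Chance of none |
|---|---|---|---|---|
| 5% | 0.8 | 44% | 1.6 | 19.4% |
| 10% | 1.6 | 18.5% | 3.2 | 3.4% |
| 20% | 3.2 | 2.8% | 6.4 | 0.1% |
| 30% | 4.8 | 0.3% | 9.6 | below 0.1% |

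With the planned completers instead (14 and 28 infants), the range is 14 × 0.05 = 0.7 to 28 × 0.30 = 8.4.

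**4. What a Mann-Whitney test could show.** With m cases against the 16 infants of Group 1, the smallest attainable exact two-sided p is 2 / C(16 + m, m):
- m = 1: 2 / 17 = 0.118
- m = 2: 2 / 153 = 0.013
- m = 3: 2 / 969 = 0.0021

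With one case the test cannot reach 0.05 whatever the data.

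**5. Exposure.** Groups 2 and 3 have monthly or weekly sessions for six months, and Group 1 has none (section 2.8). If T2 cases come from Groups 2 and 3 and are compared with Group 1, any difference at T1 or T2 is mixed with exposure to the sessions.

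**The case against.** **Some assayed infants may have ASD.** A reader might infer that no child with ASD is assayed, so that a case group is impossible. The article does not support that. Section 2.5.1.2 plans ADOS-2 and, at T2, an ADI-R algorithm with a clinical cut-off. An infant who meets criteria would have cytokine and miRNA samples from all three visits. This stands, and it limits the point: the case group is undefined and probably very small, not impossible. Nothing in the article makes the T2 classification the case definition.

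**The older siblings do give saliva.** The kits cover DNA, RNA and protein, and section 2.5.4 refers to a supplementary appendix that is not shown. Assays on the siblings therefore cannot be ruled out. But the article's own assay list gives them the genetic panel only, so the two sections still need to be reconciled.

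**H4 is not ignored.** One could infer that the plan fails to test H4 at all. That goes too far. H4 also seeks risk biomarkers, section 2.13 opens with comparisons among the three groups and a description of pre-post change, and section 2.5.4 plans correlations with developmental change before and after intervention. What stands is narrower: the only test named for the immunological parameters does not address change with the intervention.

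**Multiplicity and modelling.** It is tempting to add a count of chance findings among miRNAs. The article gives no number of miRNAs and no testing rule, and error control, transformation and model choice are commonly left to the analysis plan. No point is made of these.

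**Limited stakes.** These are secondary aims, and the Discussion calls the biomarker data preliminary. That is fair and bears on the weight of the point, but section 2.13 still announces a specific conclusion that the sampling does not support.

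**Conclusion.** The concern holds as a mismatch between a stated analysis and the samples listed for it. Sections 2.5.4 and 2.13 name ASD and TD children, but the study groups are defined by sibling risk and baseline signs, and the children with a known diagnosis are listed only for genetics. Any cases among the infants would rest on an unstated T2 classification: about 1 to 10 children, possibly none. That range depends wholly on the assumed rates of 5% to 30% and on 16 to 32 high-risk infants. The mismatch itself rests on the article's text and needs no assumption.

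The named contrast cannot support a claim of immunological biomarkers specific to ASD, and it does not address the intervention-change part of H4. It should be corrected. As it concerns a secondary aim, the primary outcome and the sample size are unaffected.

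**What to change.** Reconcile sections 2.5.4 and 2.13:
- Make the main cytokine and miRNA contrast a comparison of Groups 1, 2 and 3 across T0, T1 and T2, in line with the three-group comparison that opens section 2.13.
- Use ADOS-2/ADI-R classification at T2 only as a descriptive or exploratory contrast, with the criterion stated.
- Reword the claim to exploratory markers associated with study group and their change over time. Add that the groups are not randomised, so differences in change cannot be credited to the intervention alone, and that Group 3 mixes low- and high-risk infants, so group is not the same as familial risk.
- If assays of the older siblings were intended, list them in section 2.5.4.

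The cost is wording in two sections, and the main contrast needs no extra samples. The downside is that the biomarker claim becomes exploratory.

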## Discussion

3

This study aims to provide evidence on the feasibility and efficacy of an innovative and early intervention program for infants at risk of developing neurodevelopmental disorders. In this way, new findings and insights could set the basis for the future development of guidelines on managing early support and intervention for at-risk families, both in the presence and absence of specific risk signs. In fact, evidence suggests that this early and preemptive approach may substantially impact the quality of life for the families involved, reducing parental stress and improving parents’ sense of competence in their role (15, 17). In addition, from an economic standpoint, early diagnosis and intervention can lead to better developmental outcomes, which can result in a decreased need for therapies (such as psychomotor, speech, and physical therapies) and special needs services later in life, thus resulting in improved cost-effectiveness for the health care system in the long run, as already demonstrated (57). Moreover, the approach of the ERI-SIBS program is designed to include in the Italian national health system the more recent scientific literature concerning early intervention for children with neurodevelopmental disorders (58). These are the implementation of training-based interventions harnessing experience-dependent plasticity, the use of environmental enrichment's paradigm for promoting voluntary, self-initiated actions and learning, and the promotion of parent-child interactions, fostering a sense of self-competence and autonomy, a better generalization of child's learnings and the promotion of a secure bonding. Our investigation could contribute to the debate on the intensity and duration of intervention for the developmental domains of young ASD children. In fact, in a recent meta-analysis, Sandbank et al. (59) reported little robust evidence supporting the provision of intensive interventions for this population. Finally, the contribution of biomolecular, genetic, and epigenetic testing, as well as the use of technologies to collect quantitative data on joint attention and early social responses, confers a particular and innovative role to this project: it could allow the collection of preliminary data for characterising biomarkers to understand better not only the natural developmental trajectories of these children but also to identify eventual changes that can be related to clinical early intervention.

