#### Primary outcome

1.1.1

**H1:** The main hypothesis of this study is that early parent-mediated intervention in children at risk for neurodevelopmental disorders can be implemented in routine care, positively impacting early sensory-motor and socio-communicative developmental trajectories and reducing the developmental gap in children with signs of concern. For this first aim, we will use standardised, age-appropriate, and sensitive tools to define the presence of early signs suggestive of neurodevelopmental disorders and to monitor their developmental trajectories over time.

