#### Secondary outcomes

1.1.2

**H2:** Here, it is postulated that early intervention with active parental involvement can reduce parental stress and improve parental understanding of and responsiveness to a child's communication cues. This hypothesis will be tested by standardised tools that consist of scoring parental style of interaction during a free-play sequence and intercepting stress signals by an auto-administered questionnaire for parents.**H3:** An important part of our work will be analysing data about early social and joint attention behaviours in recruited children and comparing them at different time points. The hypothesis is to identify early differences between groups at baseline and to detect changes before and after the intervention. For this reason, in our study design, we decided to use technologies to collect data on quantitative measures during play-structured and laboratory sessions to understand changes in developmental trajectories.**H4:** Given the potential role of genetic and immunological mechanisms in ASD, one of the secondary aims of this study is to investigate the impact of an early intervention programme on epigenetic changes and inflammatory and immune responses. This hypothesis is based on the possibility that behavioural symptoms are related to genetic markers and biological mechanisms underlying the aetiology of ASD. It is, therefore, conceivable that certain risk biomarkers for ASD or other neurodevelopmental disorders may be present in these populations. Identifying such biomarkers may improve our understanding of genetic risk factors and biological processes underlying these conditions.

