### Interventions

2.8

Children allocated in Group 1 (Clinical Monitoring Group) won't perform any treatment, but only clinical evaluations, at the defined time points. On the contrary, children of Groups 2 and 3 will perform training according to the following guidelines.

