### Study procedures

2.11

Researchers will contact interested parents to assess eligibility and provide detailed study information. Parents will provide written consent before completing baseline assessments (T0), and based on the scores from the primary outcome measures, children will be assigned to the correct group. Infants with no signs of concern (scores at the Griffiths-3 and CSBS-ITC in the normal range), which are siblings of TD children, will be allocated to Group 1 (CM); infants with no signs of concern (scores at the Griffiths-3 and CSBS-ITC in the normal range) which are siblings of ASD children will be allocated to Group 2 (AM); infants with a quotient score below 85 using Griffiths-3 and at least one score above the “concern” cut-off using the CSBS-ITC will be allocated to Group 3 (EI). Families allocated to Groups 2 and 3 will start the intervention within one month of the baseline assessment. Families allocated to Group 1 will perform only the evaluations at different time points. Assessments will be conducted at baseline (T0), which will be when the parents give their consent and within the eight months of life of the child, after six months from the start of the intervention (T1) and after 12 months from the start of the intervention (T2). During the recruitment phase, the study's importance in developing specific guidelines for children at risk of neurodevelopmental disorders will be explained in order to improve adherence to the methodology. Participants may withdraw from the study for any reason at any time.

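### Management is fully tied to clinical group, so there is no like-for-like untreated comparator and the causal hypotheses (H1, H2, H4) and efficacy aim go beyond the design

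*Protocol article*

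**What the plan says.** **Label and aim.** Section 2.1 states: "The study is a controlled trial following the Consolidated Standards of Reporting Trials (CONSORT) guidelines". Section 3 states: "This study aims to provide evidence on the feasibility and efficacy of an innovative and early intervention program". It adds that the results could feed future guidelines and inform the debate on how intensive and how long intervention should be.

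**Hypotheses.** H1 (section 1.1.1) expects early parent-mediated intervention to be feasible in routine care while "positively impacting early sensory-motor and socio-communicative developmental trajectories and reducing the developmental gap in children with signs of concern". H2 (1.1.2) postulates that "early intervention with active parental involvement can reduce parental stress and improve parental understanding of and responsiveness" to the child's cues. H4 (1.1.2) sets out "to investigate the impact of an early intervention programme on epigenetic changes and inflammatory and immune responses".

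**Allocation.** Section 2.11: "based on the scores from the primary outcome measures, children will be assigned to the correct group". TD siblings with normal Griffiths-3 and CSBS-ITC scores enter Group 1. ASD siblings with normal scores enter Group 2. Infants with a Griffiths-3 quotient below 85 and at least one CSBS-ITC score of concern enter Group 3, whatever their family risk (section 1).

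**Management.** Group 1 infants do not "perform any treatment, but only clinical evaluations" (section 2.8). Group 2 has monthly and Group 3 weekly 90-minute sessions, each for six months (2.8.1, 2.8.2).

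**Analysis.** Section 2.13 plans comparisons between the three groups and a description of pre-post change. Section 2.6 sizes the study for ECSP-I differences between groups at each time point.

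**The concern.** A claim that an intervention reduces stress, closes a developmental gap or alters biomarkers needs some view of what similar families would have shown without it. Here each combination of risk and signs receives exactly one form of management, so an intervention effect cannot be told apart from the effect of belonging to that group. Infants also mature quickly over the 12 months of follow-up, and those selected for low scores tend to score higher on retest. If pre-post gains, or a narrowing of the distance to Group 1, were read as efficacy, guidance for at-risk families could rest on maturation, selection and population differences. The article does not acknowledge this limit.

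**Working it through.** **1. What each contrast compares** (sections 1, 2.1, 2.8, 2.11, Table 1)

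| Contrast | Management | What else differs |
|---|---|---|
| Group 2 vs 1 | monthly sessions vs none | older sibling with ASD vs TD |
| Group 3 vs 1 | weekly sessions vs none | signs at T0; for high-risk Group 3 infants, also the ASD sibling |
| Group 3 vs 2 | weekly vs monthly | signs at T0; session content (Table 1); for low-risk Group 3 infants, also no ASD sibling |

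No row holds risk and signs constant while management varies. The number of untreated infants with Group 2 status is 0 against 16 planned, and likewise 0 against 16 for Group 3. As section 2.11 is worded, infants meeting only one of the two concern criteria enter no group, so they supply no comparator either. The last row also shows that session frequency cannot be isolated. Both programmes last six months, so duration does not vary at all.

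**2. The plan's own sample size**

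Inputs (section 2.6): difference 0.8, SD 0.56, two-sided α = 0.01, power 80%. Standardised difference = 0.8/0.56 = 1.43. For a two-sample t-test, power comes from the noncentral t with 2n − 2 degrees of freedom and noncentrality (Δ/SD)·√(n/2). Power is 0.792 at n = 13 and 0.831 at n = 14, so the stated 14 per group is reproduced. For 15% drop-out, 14/0.85 = 16.47, which rounds up to 17; the plan states 16. Nothing below depends on this.

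**3. What that test responds to**

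Take n = 14 per group, α = 0.01 and an intervention effect of zero. Suppose a group difference present at T0 simply persists to T1. The sizes are assumptions, except that 0.8 is the plan's design difference.

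| Persisting difference | Noncentrality = (difference/0.56)·√7 | P(significant at T1) |
|---|---|---|
| 0.2 | 0.94 | 0.046 |
| 0.4 | 1.89 | 0.21 |
| 0.6 | 2.83 | 0.53 |
| 0.8 | 3.78 | 0.83 |

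The sized comparison detects group membership. Its result at T1 is not evidence for or against an intervention effect.

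**4. Pre-post change within one treated group**

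Paired t-test, n = 14, two-sided 0.05 (assumed), no intervention effect. Spontaneous change is g SDs of the change score (assumed), with noncentrality g·√14.

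| g | P(significant) |
|---|---|
| 0.25 | 0.14 |
| 0.50 | 0.41 |
| 0.75 | 0.74 |
| 1.00 | 0.93 |

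**5. Regression to the mean on Griffiths-3 (H1)**

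The cut-off of 85 is in section 2.11. Mean 100, SD 15, normality and the retest correlation r are assumptions.

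- Mean of infants below 85 = 100 − 15·φ(1)/Φ(−1) = 100 − 15 × 0.2420/0.1587 = 100 − 22.9 = 77.1.
- Expected gain with no intervention = (1 − r) × 22.9, which is 11.4 points at r = 0.5, 6.9 at r = 0.7 and 2.3 at r = 0.9.

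This ignores the additional CSBS-ITC criterion, so it shows order of magnitude only.

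**The case against.** **Group 1 is a control.** It is concurrent and untreated, is assessed at T0, T1 and T2 and gives saliva at all three. It carries information on maturation and repeat testing. That stands. A reader might infer that the study has no comparator at all, or that nothing could be estimated under any assumption; the documents do not support either. Comparing change in a treated group with change in Group 1 would estimate an effect if the trends were otherwise parallel. But the article does not state that assumption, and its Introduction says ASD siblings are at greater risk of abnormal developmental trajectories, which speaks against it.

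**The groups do not differ on everything.** Correct. Group 2 matches Group 1 on absence of signs. Low-risk Group 3 infants have a TD older sibling, as Group 1 does, and need not differ in recruitment route (section 2.2). Each contrast has its own confounder, but each has one.

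**The article is open about its design.** It never claims randomisation, states the allocation rule, puts feasibility first, sizes for associations and calls the biomarker data preliminary. All true. It would go too far to say that every improvement will be reported as efficacy: section 2.13 promises only description and comparisons. The word *controlled* is also not false in itself. The conflict lies between this descriptive plan and the causal wording of H1, H2, H4 and section 3.

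**Direction of bias in parental stress.** One might infer that PSI-SF in Group 3 will fall as parents adapt to news of a concern. The documents do not show this. Classification follows from the T0 scores, so if PSI-SF is taken with the T0 battery, news learned through the study comes after baseline and could raise later scores. The problem for H2 is the missing like-for-like comparator, whichever way the bias runs.

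**Conclusion.** The point holds in this form. Intervention is completely confounded with clinical group, no infant in Group 2 or 3 has an untreated counterpart of the same status, and the planned analyses cannot support H1, H2, H4 or the efficacy aim as worded. A larger sample would not remove the confounding; it would make a persisting group difference or spontaneous change more likely to reach significance.

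H1 is the most exposed, since the allocation measures are also main outcomes and regression to the mean enters directly. H2 and H4 share the confounding without that direct selection. Feasibility, satisfaction and the baseline group differences in H3 are unaffected.

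The conclusion rests on the allocation and management rules alone. The probabilities and the 2.3 to 11.4 points are illustrations under the stated assumptions, not predictions.

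**What to change.** - **Section 2.1:** state that the study is non-randomised and that group, and with it management, is determined by family risk and signs at T0.
- **H1, H2, H4:** replace the causal wording with *change during the programme*, for example change in parental stress and responsiveness during the programme (H2).
- **Section 3, and the matching sentence in the Abstract:** limit the conclusion to feasibility and descriptive change. Drop the claim to inform the debate on intensity. State that differences from Group 1 are differences between populations and not treatment effects.
- **Group 1:** keep it as a descriptive concurrent reference for maturation and repeat testing.
- **Age norms:** these may be added as a descriptive reference for normed tools. They should not replace Group 1 or be read as a control. The article gives none for PICCOLO, cytokines or miRNA, and they leave regression to the mean in Group 3 untouched.

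Cost: wording only, with no added infants, visits or procedures and no change to care. The price is a less favourable claim.
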